#### Randomization procedure

We utilized permuted block randomization with randomized block sizes (2, 4 or 6) using the R package ‘blockrand’ [34]. For each participating treatment center, we created strata for age (ten-year increments) and gender (i.e., ten strata per center). This resulted in a master randomization list with either ‘A’ or ‘B’ in each stratum. An independent employee then added an additional randomization by assigning DiSCoVR or VRelax to either A or B in the master randomization list using coin flips, once for each treatment center. Upon completing T_0_, the participants will be placed in the appropriate stratum in order of inclusion by the independent randomizer, determining their group assignment.

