#### Analysis

For our primary outcome variables (theory of mind and emotion perception), previous meta-analyses [6, 7] have found effect sizes ranging between moderate (*d =* .46, theory of mind) and large (*d* = .84, emotion perception). We therefore assumed a conservative effect size of .5. With β = .80, α = .05, two groups and three assessments, we found we would need 86 participants. Assuming a drop-out rate of 13% [35], we concluded that the sample should consist of 100 participants (50 in each group).

The groups will be compared at baseline using t-tests for normally distributed variables, and Mann-Whitney U-test or χ^2^ test for other variables. Variables with a significant baseline difference between the groups will be added to the analysis as a covariate.

We will use multilevel mixed-model linear regression analysis in accordance with the intention to treat principle, with repeated assessments (level 1) nested within participants (level 2). Time and group and their interaction term will be included as fixed effects. Treatment effects will be evaluated by examining the interaction between time and group. A random intercept will be included for the participant level to account for the repeated measures. A random slope will be included for time if this improves the model, according to the AIC value. The post-treatment and follow-up assessments will be analyzed separately, comparing each to the baseline. We will also perform a multilevel regression analysis on treatment completers, defined as people who have completed at least twelve sessions (75%) of their allocated intervention. Furthermore, moderator (e.g., clinical and demographic variables) and mediator analyses will also be conducted. Significance will be accepted at α = .05 (two-tailed); in case of multiple measurements within the same domain, a correction will be applied to α.

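### Covariates are chosen by baseline significance tests, so chance sets the adjustment, and the stratification factors are not in the stated model

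*Protocol article*

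**What the plan says.** All of the model text is in the Analysis section of the protocol article.

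- Baseline testing: "The groups will be compared at baseline using t-tests for normally distributed variables, and Mann-Whitney U-test or χ^2^ test for other variables".
- Consequence of those tests: "Variables with a significant baseline difference between the groups will be added to the analysis as a covariate". No list of candidate variables, no prognostic criterion and no limit on their number is given.
- Fixed effects: "Time and group and their interaction term will be included as fixed effects".
- Levels: "with repeated assessments (level 1) nested within participants (level 2"). There is no centre level.
- Random effects: "A random intercept will be included for the participant level to account for the repeated measures". A random slope for time is added if AIC favours it.
- Treatment effect: "Treatment effects will be evaluated by examining the interaction between time and group".
- Time points: "The post-treatment and follow-up assessments will be analyzed separately, comparing each to the baseline", so each analysis has two assessments per participant.

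Under Randomization procedure, allocation is stratified within each treatment centre: "we created strata for age (ten-year increments) and gender (i.e., ten strata per center"). Group assignment follows completion of T0 and is made by an independent randomiser.

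**The concern.** The rule has three weaknesses.

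1. **Chance decides the adjustment.** Allocation is random and follows T0, so any significant baseline difference is a chance event. The rule admits variables for being imbalanced, whether or not they predict outcome. It leaves out a strongly prognostic variable that misses p < .05.
2. **The design factors are bypassed.** Centre, age and gender were important enough to stratify on, yet they have no term in the stated model. Their only route in is a significant baseline test, and stratification works against that.
3. **The rule may do nothing.** The treatment effect is a within-person contrast. A person-level covariate added as a main effect largely cancels out of it, so a result reported as adjusted for an imbalance would in effect be unadjusted.

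At stake are whether the primary analysis is fixed in advance, and whether the word adjusted in the report means anything.

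**Working it through.** The document gives no figure for this rule, so there is none to reproduce. The only planning figure used below is the 13% drop-out, which is consistent with the stated sample size: 86 / 0.87 = 98.9, against 100 planned.

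**Step 1. How often chance selects a covariate.** The document does not say which variables are tested. A count of what is measured at baseline, outside the experience-sampling items, gives an upper figure:
- 16 background items under Demographic and clinical background;
- 17 test or scale scores: Ekman, TASIT, PSP, four PANSS scores, SIAS, two GPTS subscales, BDI, BAI, PSS, SERS, TMT-A, TMT-B and NLV.

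The total is 33. For k independent tests at .05, P(at least one) = 1 − 0.95^k, and the expected number is 0.05k.

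| k | P(at least one) | Expected number |
|---|---|---|
| 10 | 40% | 0.50 |
| 16 | 56% | 0.80 |
| 32 | 81% | 1.60 |
| 33 | 82% | 1.65 |

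The tests are not truly independent; for example, the PANSS total is the sum of its subscales. With 33 tests equally correlated at 0.3 or 0.5 (assumed), the probability falls to 69% or 53%.

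**Step 2. The stratification factors.** Four centres are named, each with ten strata, so 4 × 10 = 40 strata for 100 participants, or 100 / 40 = 2.5 per stratum. The named fixed effects are time, group and their product. Stratified blocks push the arms towards balance on centre, age and gender, so their baseline tests are less likely than others to reach significance.

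**Step 3. What a main-effect covariate does to the interaction.** With two assessments, write

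y_it = a + b·g_i + c·t + d·g_i·t + γ·x_i + u_i + e_it, with t = 0 or 1.

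For a participant with both assessments the change is

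y_i1 − y_i0 = c + d·g_i + (e_i1 − e_i0).

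The covariate term γ·x_i cancels, as does the random intercept. With complete pairs, the estimate of d is the difference in mean change, with or without x.

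**Step 4. Numerical check.** Mixed models (REML, random intercept) were fitted to simulated data with N = 100, a true interaction of 0.5, a covariate imbalanced by 0.45 SD, and 60 runs per setting. All of these values are assumptions. The residual SD was 0.6 at each assessment, so the expected SE is √(2 × 0.36 × (1/50 + 1/50)) = √0.0288 = 0.170. The outcome SD was close to 1, so shifts read roughly as SD units.

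- *Complete pairs:* adding one or two main effects changed the estimate by 0.00000. The SE was 0.1693 with and without them.
- *13% missing at the second assessment:* the mean absolute change was 0.013 with one covariate and 0.016 with two; the largest was 0.069. The SE went from 0.178 to 0.177.
- *Covariate that also predicts change (slope 0.2), complete pairs:* the expected unadjusted value is 0.5 + 0.2 × 0.45 = 0.59. The simulated mean was 0.618 unadjusted and 0.618 with the main effect. A covariate-by-time term gave 0.514.

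In the last setting an imbalance that matters is left in place by a main effect and largely removed by a covariate-by-time term.

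**The case against.** The strongest reply is that two of the charges weaken each other. If main-effect covariates leave the interaction almost unchanged, then it hardly matters for the primary result which ones chance selects. If they enter with time terms, they do act, and the charge that the rule fails at its purpose falls. This stands as a limit on the harm. Under either form, however, the rule is poor: it is nearly inert, or it makes the estimate depend on which tests happened to be significant.

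Other points on that side also stand:
- The article does not say that covariates enter as main effects. That is the natural reading of its wording, no more.
- A reader might infer that the rule cannot affect the interaction at all. That is exact only for complete pairs. The protocol plans for 13% drop-out, and participants with one assessment let a main effect move the estimate slightly.
- A reader might infer that omitting centre, age and gender loses precision in the stated model. By the algebra above, adding them as main effects there would gain almost nothing. A gain needs a different form of adjustment, and the document gives no figure for its size.
- A single figure of 82% would be too firm, because it takes all 33 variables as tested and the tests as independent.

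That an article leaves detail to the full protocol or analysis plan does not answer the main point: the selection rule is stated outright.

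**Conclusion.** The concern holds in limited form. The protocol commits to choosing covariates by post-randomisation significance tests, so chance rather than prognosis determines the adjustment set. At least one chance covariate has a probability of 40% to 82% for 10 to 33 independent tests, and less if the tests are correlated; the number tested is an assumption. The stratification factors are absent from the stated model and unlikely to enter through the rule.

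If flagged variables enter as main effects, the interaction is unchanged for complete pairs and shifts by about 0.01 to 0.02 on average with 13% missing (largest seen 0.07, under the simulation's assumptions). The rule would then not correct the imbalance that prompted it. The documents do not support a claim that the primary result is seriously biased or that a known amount of precision is lost. The rule should be changed because it is poor as written and a better one uses data already collected.

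**What to change.** Delete the baseline tests and the covariate rule, and report baseline data descriptively by arm.

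For every outcome, prespecify its T0 score, centre, age (continuous) and gender as separate terms in a baseline-adjusted model of the post-baseline score. With 2.5 participants per stratum on average, the 40 strata should not be fitted as a full cross. If the stated repeated-measures model is kept, enter centre, age and gender with covariate-by-time terms; the T0 score is already a response there and should not also be a covariate. Adding the factors as main effects only would not be enough.

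No new data are needed. The cost is a few degrees of freedom and, with the baseline-adjusted model, a change in the form of the primary model. That is more than a wording edit in a prospectively registered trial, so it should be documented as a change made before the outcome data are unblinded.

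### Testing the time-by-group interaction with free baseline means is valid but inefficient: under equal SDs it gives up (1 − ρ)/2 of the precision that adjustment for the T0 score would keep

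*Protocol article*

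**What the plan says.** All of the following is in the protocol article.

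- **Model (Analysis).** "Time and group and their interaction term will be included as fixed effects". On random effects: "A random intercept will be included for the participant level to account for the repeated measures". A random slope for time is added if AIC favours it.
- **Test (Analysis).** "Treatment effects will be evaluated by examining the interaction between time and group".
- **Time points (Analysis).** "The post-treatment and follow-up assessments will be analyzed separately, comparing each to the baseline". Each contrast therefore comes from a model with two occasions.
- **Covariates (Analysis).** "Variables with a significant baseline difference between the groups will be added to the analysis as a covariate". Nothing else in the section adjusts for the baseline score of the outcome.
- **Timing (Randomization procedure).** "Upon completing T_0_, the participants will be placed in the appropriate stratum in order of inclusion by the independent randomizer". Allocation follows the baseline assessment.
- **Sample size (Analysis).** "We therefore assumed a conservative effect size of .5", and "With β = .80, α = .05, two groups and three assessments, we found we would need 86 participants". This is raised to 100 for 13% dropout. No SD and no correlation between assessments is given for either Ekman 60 Faces or TASIT.

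**The concern.** A group main effect in a T0/T1 model lets the two arms have different T0 means. Because T0 is measured before allocation, any T0 difference is chance. The planned contrast subtracts that difference in full, although only a fraction ρ of it (under equal SDs) is expected to persist to follow-up. The excess is noise in the estimated effect.

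The covariate rule looks like a safeguard but is not one here. A covariate that does not change over time, entered as a main effect, shifts both occasions of a participant equally and so drops out of the interaction. This is true even of the baseline score itself.

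What is at stake is power for two primary outcomes in a trial of 100 people. The loss is avoidable with data that Table 1 already schedules.

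**Working it through.** **Inputs.** From the Analysis section: d = .5, two-sided α = .05, power .80 (printed there as β), two groups, three assessments, 86 evaluable, 13% dropout. Assumed, because the article does not give them: the correlation ρ between T0 and follow-up, equal SDs at T0 and follow-up (set to 1), and d expressed on the raw-score SD.

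**1. The plan's own figure.** N = 86 is reproduced by the between-groups main effect of a repeated-measures ANOVA with f = .25 and m = 3:

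λ = f²·N·m / [1 + (m − 1)ρ] = .0625 × 86 × 3 / (1 + 2 × .5) = 8.06, with 1 and 84 df, giving power .801.

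The required N is 78 at ρ = .4, 86 at ρ = .5 and 96 at ρ = .6. So ρ = .5 is the value implied by the stated N. It is an inference, not a statement in the article, and was not set separately for each outcome.

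**2. What the planned model estimates.** In a simulated complete data set (43 per arm, two occasions, ρ = .5):

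| Analysis | Estimate | SE |
|---|---|---|
| Difference in raw mean change | .58296 | – |
| Time, group, interaction | .58296 | .175 |
| Same, plus an unrelated covariate as main effect | .58296 | .175 |
| Same, plus the T0 score as main effect | .58296 | .169 |
| Common T0 mean (no group main effect) | .600 | .157 |
| ANCOVA on the T0 score | .599 | .162 |

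The first four estimates are identical, so the covariate rule does not turn the interaction into a baseline-adjusted effect.

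**3. Precision lost.** Per-participant variance, SD = 1:

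- change score: 2(1 − ρ)
- baseline-adjusted: 1 − ρ²
- ratio: (1 − ρ²) / [2(1 − ρ)] = (1 + ρ)/2
- share of inverse variance lost: 1 − (1 + ρ)/2 = (1 − ρ)/2

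Power uses the noncentral t with 43 per arm and d = .5. N is the evaluable total for 80% power.

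| ρ | Variance, change | Variance, adjusted | Precision lost | Power, change | Power, adjusted | N, change | N, adjusted |
|---|---|---|---|---|---|---|---|
| .3 | 1.40 | .91 | 35% | .49 | .67 | 178 | 118 |
| .5 | 1.00 | .75 | 25% | .63 | .75 | 128 | 98 |
| .6 | .80 | .64 | 20% | .73 | .82 | 104 | 84 |
| .7 | .60 | .51 | 15% | .84 | .89 | 78 | 68 |
| .8 | .40 | .36 | 10% | .95 | .97 | 54 | 48 |
| .9 | .20 | .19 | 5% | >.99 | >.99 | 28 | 26 |

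On the SE scale the gain is smaller: adjustment shortens the SE by 1 − √.75 = 13.4% at ρ = .5 and by 1 − √.85 = 7.8% at ρ = .7.

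**4. With dropout.** If 13% have no T1 score but their T0 data stay in the model, the planned interaction is no longer exactly the completers' change difference. The loss against a common-T0-mean model is then 22.5% at ρ = .5, 17.9% at .6, 13.3% at .7 and 8.8% at .8.

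**5. Unequal SDs.** Take SD 1 at T0 and 1.25 at follow-up, with ρ = .5, so the covariance is .625. A random intercept alone forces a common variance, (1 + 1.5625)/2 = 1.281, and so a slope of .625/1.281 = .488 on the T0 difference. For the common-T0-mean model:

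- model-based variance: 1.281 × (1 − .488²) = .976
- true variance: 1.5625 + .488² − 2 × .488 × .625 = 1.191
- SE ratio: √(.976/1.191) = .906, so a nominal 5% test has type I error of about 7.6%

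The covariance structure therefore matters for the remedy. In the planned model with complete data, the point estimate does not depend on it.

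**The case against.** The strongest reply is that nothing here is wrong in the sense of invalid. Allocation follows T0, the change contrast is unbiased over randomisations, and its SE already reflects chance imbalance. That stands. A reader might infer that the planned effect is biased by baseline differences; the documents do not support that reading.

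A reader might also infer a fixed loss of 15–25% on both primary outcomes. That range needs ρ between .5 and .7 for each test. The article gives no ρ, and TASIT alternates parallel versions, so its ρ may differ from that of Ekman 60 Faces. Over ρ from .3 to .9 the loss runs from 35% to 5%.

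Nor can one conclude that the trial is underpowered whatever ρ is: at ρ = .7 the planned test already has 84% power. The shortfall at lower ρ is due in large part to N = 86 resting on a between-groups average over three assessments rather than on the interaction tested, which is a separate matter.

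Two technical objections also stand. The ratio (1 + ρ)/2 requires equal SDs: with an SD ratio of 1.5 and ρ = .7 the variances are 1.150 (change) and 1.148 (ANCOVA), so almost nothing is gained. And removing the group main effect while keeping only a random intercept can inflate type I error, as step 5 shows.

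What the reply does not remove is that the stated model leaves precision unused whenever SDs are similar and ρ is below 1, and that the covariate rule does not recover it.

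**Conclusion.** The point holds as one of efficiency. As written, the primary contrast is the raw change difference when data are complete, and adjustment for the T0 score would be more precise by an amount that depends on an unstated ρ. At the implied ρ = .5, a quarter of the precision is lost and power at 86 evaluable participants is 63% rather than 75%. At ρ = .7 the difference is 84% against 89%, and beyond that it hardly matters. These figures assume equal SDs at T0 and follow-up, d = .5 on the raw-score SD, and complete data; 13% dropout reduces the loss slightly. The direction is secure under equal SDs, but the size for each outcome is not known from the article. It is an improvement worth making, not a correction of an invalid analysis.

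**What to change.** For each outcome measured at T0, estimate the T1 and T2 group differences adjusted for the T0 score of that same outcome, whether or not the arms differ significantly at baseline. Either of two forms will do:

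- **ANCOVA** at T1 and at T2, with the T0 score as covariate. This keeps the separate analyses of the two follow-ups.
- **Constrained longitudinal model**: a common T0 mean, time, and group-by-T1 and group-by-T2 terms, with an unstructured covariance across the three assessments instead of a random intercept alone.

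They are not strictly interchangeable. ANCOVA omits participants with no post-baseline score. The constrained model keeps them, but relies on its covariance being correctly specified and replaces the two separate analyses with one. The choice should be written down before unblinded data are analysed. The cost is a change to the analysis text and code; no additional data or participants are needed.

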**Methods:**

In total 100 people with a psychotic disorder and deficits in social cognition will be recruited for this multicenter randomized controlled trial (RCT). Participants will be randomized to VR SCT (DiSCoVR) or VR relaxation training (VRelax; active control). DiSCoVR is a 16-session individual SCT, consisting of three modules: 1) emotion perception (recognizing facial emotions in a virtual shopping street); 2) social perception and theory of mind (observing social interactions between virtual characters and assessing their behavior, emotions and thoughts); and 3) application of higher-order social cognition in social interaction (role-playing personalized situations in VR). People receiving VRelax complete sixteen individual sessions, in which they receive psycho-education about stress, identify personal stressors, learn relaxation techniques, and explore relaxing immersive virtual environments.

Assessments will be performed at baseline, post-treatment, and 3-month follow-up. Primary outcomes are emotion perception (Ekman 60 Faces), social perception and theory of mind (The Awareness of Social Inference Test). Secondary outcomes include social functioning (Personal and Social Performance Scale), experiences and social interactions in daily life (experience sampling of emotions, social participation and subjective experience of social situations), psychiatric symptoms (e.g., depression, perceived stress, anxiety, positive and negative symptoms) and self-esteem.

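### With T1 and T2 each fitted against baseline alone, the AIC rule for a random time slope cannot do its job, and the T2 model ignores T1 where T2 is missing

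*Protocol article*

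**What the plan says.** The abstract sets out three visits: "Assessments will be performed at baseline, post-treatment, and 3-month follow-up". The Analysis section then describes a two-level model, "with repeated assessments (level 1) nested within participants (level 2"). Its fixed part is given as "Time and group and their interaction term will be included as fixed effects", and the treatment effect is read from the interaction. For the random part, the section says "A random intercept will be included for the participant level to account for the repeated measures", followed by "A random slope will be included for time if this improves the model, according to the AIC value". The sentence after that reads "The post-treatment and follow-up assessments will be analyzed separately, comparing each to the baseline".

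The section states no joint three-visit model for the treatment effect, no time coding, and no statement on whether the intercept and slope may correlate. The sample size paragraph, by contrast, counts all three visits: "With β = .80, α = .05, two groups and three assessments, we found we would need 86 participants".

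The Drop-out section adds that people who stop treatment are asked to stay in the assessments, and that those who miss T1 are still approached for T2.

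**The concern.** Two adjacent sentences do not fit together. A random slope describes how participants differ in their change over time. To separate that from residual noise, the model needs more occasions than a baseline and one follow-up. If each follow-up is fitted only with baseline, the choice between models with and without a slope is made where the slope variance cannot be told apart from the residual variance. Analysts could then get a refused fit, a boundary warning or an arbitrary split of variance. They might also report slope heterogeneity that the data cannot show.

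The second matter is durability, a stated aim of the trial. A model of T0 and T2 alone makes no use of T1 for a participant who attended T1 and then missed T2. The T2 estimate then rests on a stronger missing-data assumption than the collected data require.

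**Working it through.** **Inputs from the article.** Three visits; separate analysis of each follow-up against baseline; random intercept always, slope by AIC; 50 per arm; 13% drop-out; effect size .5. The article gives no correlations between visits and no missingness pattern, so those below are assumptions.

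**1. The plan's own figure.** With f = .25 (that is, d = .5), m = 3 visits and an assumed correlation of .5, the between-groups repeated-measures formula gives λ = f²·N·m / (1 + (m − 1)ρ) = .0625 × 86 × 3 / 2 = 8.06, and power .801 at two-sided α = .05. Then 86/.87 = 98.9, so 99, which fits the stated 100. The 86 can thus be reproduced by a three-visit calculation, whereas each treatment-effect model as written uses two visits. The article does not name its formula, so this shows only that the figure is consistent with three visits.

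**2. Identification with two visits.** Code time 0/1, with intercept variance a, slope variance b, their covariance c and residual variance s:
- Var(T0) = a + s
- Cov(T0, follow-up) = a + c
- Var(follow-up) = a + 2c + b + s

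That is three equations for four unknowns. Take both variances as 1 and the covariance as .5. Every choice of s from .1 to .4 reproduces this matrix exactly, with a = 1 − s, c = s − .5 and b = 1 − 2s:

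| s | a | c | b |
|---|---|---|---|
| .1 | .9 | −.4 | .8 |
| .2 | .8 | −.3 | .6 |
| .3 | .7 | −.2 | .4 |
| .4 | .6 | −.1 | .2 |

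The likelihood is the same in all four rows, while the slope variance runs from .8 to .2.

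**3. Uncorrelated slope (c = 0).** Under 0/1 coding, b = Var(follow-up) − Var(T0), which is estimable but is only a difference between the two variances. Under −.5/+.5 coding, both variances equal a + b/4 + s and the covariance is a − b/4: two distinct equations for three unknowns.

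**4. What AIC then compares.** The random-intercept model forces equal variances at the two visits. Adding a correlated slope only frees them, at a charge of two extra parameters. In a simulation with 50 per arm, correlation .5 and 4,000 replicates, AIC chose the correlated slope in about 5% of trials with equal SDs, 53% with the follow-up SD 1.2 times baseline, and 96% at 1.4 times.

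**5. Effect on the treatment estimate.** With complete data the interaction is the difference between arms in mean change, with or without the slope. A trial fit gave the same SE, .2297, both ways.

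**6. Precision at T2.** Take unit SDs, 50 per arm with 13% missing T2 (43.5 observed), and T1 present for all who miss T2. Let V = 2 − 2ρ02 be the variance of the T2−T0 change, and E the residual variance of T2 given the earlier visits in the model. The contrast variance is 2 × [E/43.5 + (V − E)/50]. With correlations T0–T1 .6, T0–T2 .6 and T1–T2 .8, V = .8:
- Separate: E = 1 − .6² = .64; variance 2 × (.01471 + .00320) = .0358; SE .189; power 75% for a .5 SD effect.
- Joint: R² = (.36 + .64 − 2 × .6 × .6 × .8)/(1 − .36) = .6625, so E = .3375; variance 2 × (.00776 + .00925) = .0340; SE .184; power 77%.

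The ratio is .95. Across the five sets of correlations tried it was .95 to .99. It is 1.00 if those who miss T2 also lack T1.

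**7. Bias at T2 (true effect .50 SD).**

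| Assumed dropout before T2 | Separate T0/T2 model | Joint model |
|---|---|---|
| 13%, depends on T1 change in one arm only | .55 to .57 or .43 to .46, by direction | about .50 |
| 13%, depends equally in both arms on within-arm T1 change | .50 to .51 | about .50 |
| 9 to 15%, same rule on the T1 score in both arms | .46 | .50 |

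The first two rows use correlations .6/.5/.7 (T0–T1, T0–T2, T1–T2); the third uses .6/.6/.8.

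**The case against.** The strongest reply is that the treatment analysis survives. The random intercept is always in the model and the slope enters only on condition. The fixed effects and the tested interaction are set in advance, and the SE did not move in the trial fit. That stands. A reader might infer that the primary model cannot be fitted at all, or that the treatment effect would be chosen after seeing outcomes; the text supports neither. AIC here governs only the covariance part.

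The four-against-three count also assumes that intercept and slope may correlate, which the article does not say. This is fair, but an uncorrelated slope helps only under particular time codings, and no coding is fixed.

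The sentence on separate analysis could mean two contrasts from one three-visit model, and the sample size does count three visits. On that reading a linear slope is identified (four parameters, six covariance elements) and T1 is used. The wording points the other way, so it needs correcting in either case. Random effects for each level of categorical time would still fail: seven parameters for six elements.

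On missing data, someone who misses T1 but attends T2 is fully used in the T0/T2 model, so the Drop-out rule on contacting such people is no evidence of loss there. Asking treatment drop-outs to stay in assessment also limits missingness. Separate comparisons with baseline are a legitimate, if less efficient, choice.

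**Conclusion.** The concern holds for the slope rule and, more modestly, for the T2 analysis. On the plain reading, the AIC step cannot assess whether participants differ in their change; it registers only unequal variances at two visits. That follows from the parameter count and needs no assumption about the data beyond separate fits. The time-by-group estimate itself remains available.

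For T2, the separate model requires missingness to be unrelated to T1 given baseline. The precision cost is about 1 to 5% of variance at 13% missing, under the assumed correlations and with T1 seen in those who miss T2. A reader might infer that the durability effect would be overstated by some 10% (.55 against .50). The article does not support that: it gives no dropout pattern, and plausible patterns move the estimate up, down or not at all.

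**What to change.** Delete the random-slope and AIC sentence. Fit one model per outcome to T0, T1 and T2, with time as a categorical factor, group, their interaction and a pre-specified within-participant covariance, for example unstructured. Report two group contrasts from it: T1 minus T0 and T2 minus T0. Both planned comparisons are kept, and T1 informs the T2 estimate where T2 is missing. The degrees-of-freedom method can be left to the SAP.

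If a single three-visit model was already intended, say so and reword the sentence on separate analysis. In that case also state the random part, because a full set of random effects on categorical time is not identified.

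The cost is analysis wording only: no new data, visits or participants.
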